**Figure 1 figure1:**
[figure not shown]
Flow diagram of the trial.

### Eligibility Criteria

The target population will be adult patients with COVID-19 who have been discharged from the hospital and are still experiencing respiratory impairments. Patients will be recruited from Hong Kong. Inclusion criteria will include (1) age ≥18 years; (2) discharged from hospital for no less than 4 weeks; (3) percentage of predicted forced vital capacity (FVC) <90% or a percentage of predicted carbon monoxide diffusing capacity <90% [17]; (4) smartphone user; (5) able to communicate in Cantonese or Mandarin. Exclusion criteria will include (1) being pregnant or planning to become pregnant in the coming 6 months; (2) having acute exacerbations in the 12 weeks preceding recruitment; (3) having any contraindications for exercise (eg, physical disability, uncontrolled mental disorders, unstable heart disease, inability to perform muscle strength tests) [18]. The last two exclusion criteria will be evaluated by a physician.

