### Randomization and Allocation Concealment

Participants will be randomly and equally assigned to the four groups using block randomization [19]. The random allocation sequence will be computer generated by a blinded statistician outside of the research team, who will use randomly mixed block sizes of 4 and 8 and conceal the randomization procedure from the research team. The results of the allocation will be randomly coded with an identification number according to the random number table. An investigator will dispense the identification numbers according to the order of the patient’s recruitment and will not be allowed to arbitrarily alter the numbering.

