#### Chinese Herbal Medicines

The Chinese herbal formula of Modified Bai He Gu Jin Tang (including Rehmanniae Radix 10 g, Rehmanniae Redix Praeparata 10 g, Ophiopogonis Radix 10 g, Lilii Bulbus 15 g, Paeoniae Radix Alba 10 g, Angelicae Sinensis Radix 10 g, Fritillariae Thunbergii Bulbus 5 g, Glycyrrhizae Radix et Rhizoma 10 g, Platycodonis Radix 15 g, and Salviae Miltiorrhizae Radix et Rhizoma 15 g) will be prescribed in granules. The rationale for the formula selection is as follows: (1) based on the syndrome differentiation, pulmonary fibrosis post–COVID-19 appears as qi-yin deficiency of the lung [32]; (2) a previous study has shown that many herbs using this formula and Salviae Miltiorrhizae Radix et Rhizoma have antifibrosis effects [33]; and (3) Bai He Gu Jin Tang has the effects of nourishing lung qi and ying deficiency [34]. Therefore, the formulation of Bai He Gu Jin Tang was modified to match the therapeutic purpose. A dose of 10 g per day (5 g, twice per day) will be ingested. Patients will dissolve a sachet of granules (5.0 g) in 200 ml of hot water twice per day after breakfast and dinner, 7 days per week, for 3 months. The entire manufacturing process will be in strict compliance with the standards of good manufacturing practice.

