### Outcomes

Table 2 lists a description of the outcomes and other measures, which are not exhaustive. All measurements will be recorded at baseline and repeated at the 13th and 25th weeks of the study. Patients will be assessed for risk prior to data collection. Further information from patients using appropriate data collection methodologies, including clinical symptoms, treatment history, comorbidities, physical activity, nutrition, and other potential variables, will be obtained and adjusted for during data analysis.

**Table 2 table2:** Description of the outcome measures.

Measure		Outcomes
Cardiorespiratory fitness		Six-minute walk test Performance time test
Dyspnea		Borg Category-Ratio 0-10 Scale (Borg Dyspnea Scale)
Body composition		BMI Waist circumference Stature Body mass Segmental muscle mass Anatomical circumference
Lung function test		Forced vital capacity Forced expiratory volume 1 Forced expiratory volume 1/forced vital capacity Fractional exhaled nitric oxide DLCO^a^
Cardiopulmonary exercise test/blood gas		VE^b^ VCO_2_^c^ VO_2_^d^/PCO_2_^e^ PO_2_^f^

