### Safety Observations

During the trial, each participant will receive safety monitoring. All adverse events will be forwarded to the ethics committee. They will review all documented harms during the trial and adjudicate them with regard to causality. The observations are listed below:

Vital signs: Body temperature, heart rate, blood pressure, and respiration (once at each follow-up visit)Blood routine, urine routine, stool routine plus occult blood (once before and after treatment, respectively; twice in total)Hepatic function (alanine aminotransferase, aspartate aminotransferase, total bilirubin, alkaline phosphatase, gamma-glutamyl transferase), renal function (serum creatinine, blood urea nitrogen) (once before and after treatment, respectively; twice in total)Electrocardiogram (once before and after treatment, respectively; twice in total)Severity and incidence of adverse events (recorded in detail at any time)

The schedule for the enrollment, interventions, and assessment is summarized in Table 3.

**Table 4 table3:** Schedule of enrollment, interventions, and assessments in the trial.

Time point		Study period (week)				
		Enrollment		Allocation	Post-allocation	Follow-up
		Washout (–3 to –1)	Run-in (–1)	0	12	12

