**Enrollment**						
	Eligibility screen	✓				
	Informed consent	✓				
	Randomization			✓		
	Allocation			✓		

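### The printed exclusion criteria screen for contraindications to exercise but not to the herbal formula, which half of participants (86 of 172) are randomised to take

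*Protocol article*

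**What the plan says.** **Eligibility Criteria** prints three numbered exclusions: pregnancy or a planned pregnancy within 6 months, an acute exacerbation in the 12 weeks before recruitment, and "having any contraindications for exercise (eg, physical disability, uncontrolled mental disorders, unstable heart disease, inability to perform muscle strength tests". It then names who judges them: "The last two exclusion criteria will be evaluated by a physician".

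**Randomization and Allocation Concealment** gives equal allocation: "Participants will be randomly and equally assigned to the four groups using block randomization". Under Study Design, two of those groups take the herbs (herbs with exercise, and herbs alone).

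**Chinese Herbal Medicines** fixes a formula of ten herbs: "A dose of 10 g per day (5 g, twice per day) will be ingested", every day of the week for 3 months. Under Waiting List Control, the waiting list group is offered the herbs after the week 25 measurements.

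The checks planned before treatment are in other sections:

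- **Outcomes** has a general check: "Patients will be assessed for risk prior to data collection". For clinical background it states a use in analysis: "treatment history, comorbidities, physical activity, nutrition, and other potential variables, will be obtained and adjusted for during data analysis".
- **Safety Observations** lists hepatic tests, an ECG and "renal function (serum creatinine, blood urea nitrogen) (once before and after treatment, respectively; twice in total".
- **The schedule table** has a row "Eligibility screen", ticked in weeks –3 to –1. Its Safety row is ticked at washout, run-in and week 0, and again later.

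**The concern.** Exercise and herbs are each given to two of the four groups, so the two interventions reach equal numbers of participants. The screening is not equal. A patient unsuited to exercise is removed by a physician before randomisation, but no matching rule is printed for a patient unsuited to the herbs.

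What is at stake is participant safety. The allocation is random, so any eligible patient may be sent to a herb group. Adverse-event review and the Data and Safety Monitoring Board respond once the trial is under way and cannot keep an unsuitable patient out. The tests that could do so are planned, but nothing printed says what follows from an abnormal result.

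**Working it through.** **1. How many are allocated to the herbs.** Inputs: 172 participants in total, 43 per group (Sample Size Calculation); equal allocation to four groups; two groups on herbs during the study.

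- Per group: 172 / 4 = 43, which matches the stated figure.
- On herbs within the study: 2 × 43 = 86, and 86 / 172 = 50%.
- Including the waiting list after week 25: 3 × 43 = 129, and 129 / 172 = 75%. The point uses the smaller count because the later supply falls after the study period.

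The protocol calls 172 preliminary, so 86 may change. The 50% share follows from equal allocation and does not.

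**2. Whether any printed exclusion covers the herbs.**

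| Exclusion | Tied to exercise? | Tied to the herbs? |
|---|---|---|
| 1. Pregnancy or planned pregnancy | No | Not stated; may protect herb recipients incidentally |
| 2. Recent acute exacerbation | No | No |
| 3. Contraindications | Yes, with four examples | No |

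**3. Whether another section closes the gap.**

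| Printed check | Before treatment? | Printed as a ground for exclusion? |
|---|---|---|
| General risk assessment (Outcomes) | Yes, before data collection | No; content not specified |
| Treatment history and comorbidities (Outcomes) | Timing not stated | No; the stated use is adjustment in analysis |
| Hepatic and renal tests, ECG (Safety Observations) | Yes, once before and once after | No |
| Safety row of the schedule table | Yes, washout to week 0 | No |
| Adverse-event review and DSMB | No; they act during the trial | No |

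So checks before exposure do exist. What is missing in print is the link from those checks to eligibility.

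**4. Whether the gap has a statistical consequence.** The planned size reproduces. A two-sample t test with d = 0.8, two-sided 0.05 and 34 per group has power 0.9015 (33 gives 0.8926), and 34 / 0.8 = 42.5, rounded up to 43; 4 × 43 = 172.

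Suppose, as an assumption with no basis in the document, that k = 0 to 4 of the 43 patients in a herb group are found unsuitable, drop out and are given their baseline values. Take the control group as unchanged and the SD as constant. Then d becomes 0.8 × (1 – k/43), with all 43 still analysed:

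| k | d | Power, 43 per group |
|---|---|---|
| 0 | 0.800 | 95.6% |
| 1 | 0.781 | 94.8% |
| 2 | 0.763 | 93.8% |
| 3 | 0.744 | 92.7% |
| 4 | 0.726 | 91.4% |

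Every value stays above the planned 90%, before any other dropout. The calculation gives no ground for a claim about power.

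**The case against.** **This is an article, and the full protocol may hold the criterion.** The exclusions are introduced with open wording that leaves room for more. This stands as a limit on confidence. It does not dispose of the point, because articles normally print eligibility criteria, and this one numbers them, gives examples for exercise and names the evaluator.

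**Safeguards before exposure are printed.** Risk assessment, hepatic and renal tests and an ECG all come before the herbs are taken, and pregnancy is excluded for everyone. This stands too. A reader might infer that nothing protects herb recipients until an adverse event occurs, and the document does not support that. The gap is narrower: no printed rule turns a planned result into an exclusion.

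**No contraindication is shown.** The document names no condition or medicine that rules out this formula, and gives no figure for how many patients would have one. This is correct, so none is asserted here.

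**A statistical harm is tempting to infer.** A reader might argue that unsuitable patients would be lost from the herb groups alone, use up the dropout allowance and, with baseline values imputed for dropouts, pull the herb effect towards zero. The document does not support this, for four reasons:

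- Any number of such patients is invented.
- The two mechanisms are incompatible: a patient cannot both be lost from the evaluable 34 and be kept among the 43 by imputation.
- Stopping the herbs is not the same as dropping out. The plan applies intention-to-treat and uses baseline values only for dropouts.
- The effect size of 0.8 comes from a meta-analysis of exercise, and the protocol says herbal effects were not considered in it.

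Any dilution from baseline values would in any case come from the imputation rule, which is a separate matter from eligibility.

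**Conclusion.** The point holds as a minor, low-cost patient-safety improvement. As printed, the contraindication rule covers one of the two randomised interventions, and 86 of 172 participants (50%) are allocated to the other without a matching rule. That figure counts those to whom the gap applies; it says nothing about how many are unsuitable, which could be none. No effect on power or bias is claimed.

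The conclusion rests on two assumptions: that the printed list is the working list, and that a physician could judge some patients unsuitable for the formula. If the full protocol already has such a criterion, all that remains is to confirm it.

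**What to change.** Extend exclusion 3 so that it reads: any contraindications for exercise or the study herbal formula. The physician who already evaluates this criterion should do so before allocation, using treatment history, comorbidities and the planned baseline hepatic and renal tests and ECG. Clinicians should set the list of contraindications and any thresholds, since the document offers no basis for them.

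**Cost.** A phrase in an existing criterion, clinical agreement on the list, a few extra screen failures and a short wait while baseline blood results are read. The schedule already has weeks –3 to –1 before allocation. Results states that recruitment has started, so the change needs an amendment and helps only patients not yet randomised. The sample size formula is unaffected.

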### Randomization and Allocation Concealment

Participants will be randomly and equally assigned to the four groups using block randomization [19]. The random allocation sequence will be computer generated by a blinded statistician outside of the research team, who will use randomly mixed block sizes of 4 and 8 and conceal the randomization procedure from the research team. The results of the allocation will be randomly coded with an identification number according to the random number table. An investigator will dispense the identification numbers according to the order of the patient’s recruitment and will not be allowed to arbitrarily alter the numbering.

### Blinding

One copy of the blind codes will be held by the project-responsible unit. The investigator operating the allocation of patients will not be involved in the intervention delivery, outcome measurements, or data analysis. The results of the allocation (being in the intervention or control groups) will be concealed from patients due to the waiting list control design, where patients in the control group will also receive a type of intervention and therefore will not know they are control participants. In addition, investigators assessing effects and those analyzing the data will also be blinded from the allocation.

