## Methods

### Study Design

The proposed study will be a triple-blinded randomized controlled trial comprising four groups: (1) a cardiorespiratory exercise plus Chinese herbal medicines group, (2) a cardiorespiratory exercise group, (3) a Chinese herbal medicines group, and (4) a waiting list group. The target population will be postdischarge adult patients recovering from COVID-19 who were diagnosed with pulmonary impairments. Recruitment will take place in Hong Kong via our International Rehabilitation Network Center for Patients With COVID-19. The proposed rehabilitation period will last for 12 weeks, with a 12-week follow-up [14]. Primary outcomes will include the clinical symptoms of pulmonary fibrosis (dyspnea, fatigue, lung function, blood oxygen levels, immune function, blood coagulation, and related blood biochemistry). Blood biochemistry will be further analyzed using unique metabolomics techniques to identify potential synergies related to immune function response to the interventions [15]. We will investigate glucose metabolism and its association with the degree of infection and prognosis. We will also profile the gut microbial metabolome to establish associations between (virus-induced) dysbiosis and the outcomes of COVID-19 infection. Pulmonary function tests will be completed using clinical spirometry, as outlined by the American Thoracic Society. Blood gas levels, immune function, and coagulation levels of the patients will be measured pre- and post-intervention in venous blood samples [16]. The trial has been registered on ClinicalTrials.gov (NCT04572360). A flow diagram of the trial is shown in Figure 1.

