#### Waiting List Control

The waiting list control sign will be adopted to conceal the allocation results from the patients as well as to reduce selection and confounding bias and increase the participants’ adherence to the study. Patients in the waiting list control group will receive no treatment in the study period (including a 12-week intervention period and a 12-week follow-up period). However, they will receive Chinese herbal medicines after the completion of the study (ie, after the third wave of measurements in the 25th week).

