#### Dyspnea

Dyspnea is a common exercise-induced symptom of disease and usually occurs in patients with pathophysiology that results in inefficient gas exchange and ventilator impairments. The Borg CR10 Scale (Borg Dyspnea Scale) will be used to rate the dyspnea and overall fatigue levels of the patients at the beginning and end of the 6MWT. The scale will also be used during the cardiopulmonary exercise test (CPET).

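### The trial is labelled triple-blinded, but waiting-list patients are untreated at every post-baseline assessment and no placebo or sham is described, so participants are not blinded

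*Protocol article*

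**What the plan says.** The Abstract and the Study Design section use the triple-blinded label; the latter states: "The proposed study will be a triple-blinded randomized controlled trial comprising four groups".

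The Blinding section names three blinded parties. For patients, the only reason given is the waiting-list design: "patients in the control group will also receive a type of intervention and therefore will not know they are control participants". For the other two it states that "investigators assessing effects and those analyzing the data will also be blinded from the allocation".

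The Waiting List Control section repeats the purpose, saying that the design "will be adopted to conceal the allocation results from the patients". It then states what this group gets: "Patients in the waiting list control group will receive no treatment in the study period". It spells out that this covers both the 12-week intervention and the 12-week follow-up, and that herbal medicine starts only after the third wave of measurements in week 25. The schedule of enrollment, interventions and assessments agrees, since the waiting-list row carries no intervention mark.

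The other arms receive 36 supervised tele-exercise sessions, herbal granules ("Patients will dissolve a sachet of granules (5.0 g) in 200 ml of hot water twice per day"), or both.

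The Abstract and Study Design list dyspnea and fatigue among the primary outcomes. On their measurement, the Dyspnea section says: "The Borg CR10 Scale (Borg Dyspnea Scale) will be used to rate the dyspnea and overall fatigue levels of the patients".

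**The concern.** Patient blinding is stated as a fact, with a reason, and another section of the same article contradicts the reason. A treatment that starts after the last outcome measurement cannot hide from a patient, at weeks 13 and 25, that nothing has been given so far.

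This matters for outcomes that the patient scores. A blinded assessor does not protect a rating that comes from an unblinded patient. If the exercise or herbal arms report less dyspnea or fatigue than the waiting list, the trial cannot separate a treatment effect from expectation or attention. A reader who trusts the label would give those results more weight than the design can carry.

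**Working it through.** **Setting the statements side by side**

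1. Post-baseline outcomes are taken at weeks 13 and 25 (Outcomes).
2. Controls receive nothing from week 0 until after the week-25 measurements (Waiting List Control; schedule). At both assessments they are untreated and can see that they are.
3. The active arms differ visibly from controls and from each other: group sessions with instructors, granules dissolved twice a day, or both. No placebo granules, sham exercise or attention control are described, and for the waiting list the no-treatment statement rules them out.
4. Patients in all four arms therefore know what they are receiving whenever a post-baseline outcome is recorded.
5. Assessor and analyst blinding is a separate statement that nothing else in the article contradicts.

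**Which outcomes are exposed**

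- Directly exposed: Borg dyspnea and fatigue (listed as primary), and the self-reported scales for quality of life, anxiety, stress, loneliness and general mental health.
- Much less exposed: lung function, blood gases, lymphocyte counts, coagulation, biochemistry and the laboratory markers related to mood. Spirometry still depends on patient effort.

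**Illustration of size**

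The per-arm numbers come from the Sample Size Calculation, which is not in dispute and reproduces. Inputs are effect size 0.8, two-sided 0.05, power 90% and 20% dropout.

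- Normal approximation: 2 × (1.960 + 1.282)² / 0.8² = 32.8, so 33 per group. The t-test version gives 33.8, so 34 per group.
- Dropout: 34 / (1 − 0.20) = 42.5, so 43 per group.
- Total: 4 × 43 = 172, as stated.

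Now suppose that the true effect is zero and unblinded reporting shifts one patient-rated outcome by b SD against the waiting list. The size of b is an assumption, because the documents give none. For n per arm:

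δ = b / √(2/n), and P(reject) = 1 − Φ(1.960 − δ) + Φ(−1.960 − δ)

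| Assumed b (SD) | δ, n = 34 | Error, n = 34 | δ, n = 43 | Error, n = 43 |
|---|---|---|---|---|
| 0.1 | 0.41 | 7% | 0.46 | 8% |
| 0.2 | 0.82 | 13% | 0.93 | 15% |
| 0.3 | 1.24 | 24% | 1.39 | 29% |
| 0.5 | 2.06 | 54% | 2.32 | 64% |

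The column for 43 is nearer to the planned intention-to-treat analysis. That analysis fills dropouts with their baseline values, which would dilute the shift somewhat; the table ignores this.

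**The case against.** **Patients may not know the word control.** A waiting-list patient who expects treatment later may not think of themselves as a control. That does not help. The Blinding section says that what is concealed is membership of the intervention or control groups, and a patient with no sessions and no granules for 24 weeks knows that no treatment is being given. The Data Protection section adds that consent sets out the experimental procedures.

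**The article is condensed and an analysis plan may exist.** This would answer an omission. Here a property is stated and then contradicted, and no analysis plan can create patient blinding.

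**Most listed primary outcomes are instrument or laboratory measures.** This stands and limits the scope. The main hypothesis also favours the combination, which involves comparisons among active arms; the illustration covers only one comparison with the waiting list.

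**Stronger readings that the documents do not support:**

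- A reader might infer that all blinding fails. Only the participant part is contradicted. Instructors obviously know what they deliver, but the Blinding section never claims that they are blinded.
- A reader might infer that the exercise arms are trained weekly in scoring themselves on the Borg scale. The text says that the scale sets aerobic intensity and that instructions on it are given in advance. Greater familiarity in those arms is a fair inference; weekly training in rating is not stated.
- A reader might infer that every mental-health outcome is self-rated. Laboratory markers such as BDNF, corticosterone and neurotransmitter metabolites are also planned.
- A reader might infer that the primary outcome must change to FVC or DLCO and that only wording is at stake. Correcting the blinding text does not require it. The Sample Size Calculation takes its effect size from a meta-analysis of dyspnea and exercise capacity, and recruitment is under way.

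**Conclusion.** The point holds as an internal contradiction and a wrong label. The trial is, at most, assessor- and analyst-blinded, and open to participants. This conclusion rests on the text alone and needs no calculation.

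The consequence falls on the patient-rated primary outcomes, dyspnea and fatigue, and on the self-reported scales, mainly in comparisons with the untreated group. The error rates of about 13% to 24% (34 per arm) or 15% to 29% (43 per arm) depend entirely on an assumed reporting shift of 0.2 to 0.3 SD. They show that a modest shift would matter; they do not estimate the error rate of this trial. Nor does the finding condemn a waiting-list control as such: the fault is in claiming that it blinds patients.

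**What to change.** - Replace the triple-blinded label throughout with assessor- and analyst-blinded, open to participants.
- Delete the sentence in Blinding saying that controls will not know their status, and the matching statement in Waiting List Control that the design conceals allocation from patients.
- Report dyspnea, fatigue and the self-reported scales as unblinded, patient-rated outcomes, with expectation bias acknowledged.
- Base conclusions about efficacy against the waiting list mainly on the lung-function measures already collected. The first objective in the Introduction already marks pulmonary function as its primary outcome.
- Instruct patients not to tell assessors which group they are in, to protect the blinding that does exist.

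The cost is the loss of the label and more cautious conclusions on patient-rated outcomes. No extra patient or measurement is needed. Formally demoting dyspnea and fatigue would be a separate decision: it would change the outcome hierarchy during recruitment and would require the basis of the sample size to be revisited.
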